### Methods in analysis to handle protocol non-adherence and any statistical methods to handle missing data {20c}

Statistical tests will be performed according to an intention-to-treat principle. Efforts will be made in order to reduce missing data to a minimum. Missing data will be imputed using multiple imputation by chained equations. Mixed model analysis will be performed for longitudinal data.

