## Outcomes {12}

### Primary outcome measure

Primary outcome is the proportion of reoperations within 1 year after primary hernia repair. This will be calculated using the number of infants that undergo a second operation related to inguinal hernia repair within 1 year following primary repair, as a fraction of the total number of infants in that group. All participants are seen by a (fellow) paediatric surgeon at the outpatient clinic or via a digital consult 1 year after primary hernia repair. The latter is done to score development of contralateral hernia, testicular atrophy and/or recurrence.

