### Secondary outcome measures

#### Total duration of operation(s) including anaesthesia time and hospital admission(s)

Duration of operation(s) including anaesthesia time will be calculated in minutes from start of anaesthesia induction until end of anaesthesia. Length of hospital stay will be calculated as the number of days a patient is admitted to the hospital. This will be recorded by the (fellow) paediatric surgeon during each separate hospital admission/visit for inguinal hernia (repair).

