### Post intervention assessment

Primary and secondary outcomes will be assessed during hospital admission, 4 weeks after primary hernia repair and 1 year after primary hernia repair. If patients develop MCIH within 1 year after primary inguinal hernia repair, baseline and outcome assessments will also be performed during and 4 weeks after MCIH repair.

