## Sample size {14}

Data from the latest systematic review shows that the incidence of infants younger than 6 months of age who develop MCIH is 12.4% [4]. Retrospective data from the Emma Children’s Hospital AMC, where in 2000/2001 contralateral exploration was routinely performed, shows similar results: 8/92 patients did not undergo contralateral exploration and subsequently one patient (12.5%) developed MCIH. Eighty-four patients underwent unilateral hernia repair with contralateral exploration of which one patient (1.2%) developed MCIH.

The expected percentage of children requiring one or more reoperations because of MCIH in the first year following hernia repair is approximately 10%. We consider a reduction of children requiring reoperation from 10 to 2.5% as clinically relevant. A total sample size of 378 patients is needed to detect such a reduction with a power of 0.80 at a two-sided alpha of 0.05 (nQuery Advisor 7.0) [29]. Taking into account 10% loss to follow-up, we need to include 416 children.

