#### Economic evaluation

The economic evaluation will be performed from both a societal and healthcare perspective in accordance with the intention-to-treat principle. The economic evaluation will be performed with the number of second operations and quality of life as outcomes. All relevant costs (costs within the healthcare system, costs for patient and family, and costs in other sectors) will be measured, valued and analysed. Healthcare costs are costs of the intervention (unilateral hernia repair with or without contralateral exploration) and costs of treatment of complications. Costs for patient and family include travel expenses, time spending costs and costs of informal care. Costs in other sectors include productivity loss due to work absenteeism by parents/caretakers. We will use a retrospective cost questionnaire and the iMTA Productivity Cost Questionnaire (iPCQ) to measure the direct and indirect costs; 4 weeks and 1 year after primary hernia repair and, if relevant, 4 weeks after re-operation. Costs will be valued using guideline prices recommended in the Netherlands Guideline for economic evaluations in healthcare (Netherlands Health Care Institute, Diemen, 2016)

For estimating quality-adjusted life years (QALY), the patients’ EQ-5D-5L health states (reported by parents/caretakers) will be converted into utility scores using the Dutch tariff [31]. QALYs will subsequently be calculated using linear interpolation between measurement points. Missing data will be imputed using multiple imputation by chained equations [32]. Incremental cost-effectiveness ratio (ICER) will be calculated by dividing the difference in costs by the difference in effects. A cost-effectiveness ratio is calculated to present the incremental costs per re-operation prevented. A cost-utility ratio expresses the incremental costs per QALY. In order to account for the possible clustering of data, analyses will be performed using linear multilevel analyses [33]. Bootstrapping techniques will be used to estimate the uncertainty surrounding the cost-effectiveness estimates. Uncertainty will be shown in cost-effectiveness planes and cost-effectiveness acceptability curves, and sensitivity analyses will be performed to test the robustness of the study results.

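### Read as written, the general imputation rule covers reoperation status, which is missing mainly in infants with no recorded event, so the reoperation percentages and their difference can come out up to 11% too high at the planned 10% loss

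*Protocol article*

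**What the plan says.** - **Missing data.** Section {20c} of the protocol article gives one general rule: "Missing data will be imputed using multiple imputation by chained equations". It makes no exception for the primary outcome. The section Economic evaluation repeats the rule.
- **Primary outcome.** Under Primary outcome measure, the numerator is the "number of infants that undergo a second operation related to inguinal hernia repair within 1 year following primary repair", taken "as a fraction of the total number of infants in that group". Every infant is to be seen "at the outpatient clinic or via a digital consult 1 year after primary hernia repair". Section {18b} ties that 1-year visit to the primary endpoint for infants withdrawn from treatment.
- **How a reoperation becomes known.** For operating time and length of stay, the secondary outcome section says: "This will be recorded by the (fellow) paediatric surgeon during each separate hospital admission/visit for inguinal hernia (repair". Under Post intervention assessment, for an infant who develops a contralateral hernia, "baseline and outcome assessments will also be performed during and 4 weeks after MCIH repair".
- **Expected loss.** Sample size {14}: "Taking into account 10% loss to follow-up, we need to include 416 children".
- **Use of the absolute effect.** Economic evaluation: "A cost-effectiveness ratio is calculated to present the incremental costs per re-operation prevented".

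**The concern.** The two values of the primary outcome reach the database by different routes. A reoperation at a participating centre generates its own operation, admission and assessment data on the day, whether or not the family returns at 1 year. That no reoperation took place is established mainly at the 1-year contact. Status is therefore unknown mainly for infants with nothing on record, so missingness depends on the outcome itself.

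Standard chained equations assume missing at random. The model is fitted to infants with known status. Among them most reoperations are still present while a share of the event-free infants has dropped out. The reoperation rate it passes on to the lost infants is then too high. Adjusting for centre, sex, gestational age and hernia side does not cure this, because within those strata missingness still depends on the outcome.

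At stake are the two reported reoperation percentages, their difference, and the denominator of the cost per reoperation prevented. The primary odds ratio is at stake only if loss differs between arms.

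**Working it through.** **Inputs from Sample size {14} and {16a}.** Reoperation 10% (control) v 2.5% (exploration); power 0.80; two-sided alpha 0.05; 10% loss; 416 infants, 1:1, so 208 per arm.

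**Input not in the document.** The share c of lost infants' reoperations that the trial nevertheless records. The full range 0 to 1 is shown.

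**The plan's own figure.** The normal-approximation formula for two proportions gives 163 per arm without continuity correction and 189 with it; 2 × 189 = 378, as stated. 378 × 1.10 = 415.8, rounded up to 416. The inputs are therefore read correctly.

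**Upper bound: 10% of each arm has unknown status and all of these infants are event-free.** Imputation reproduces the rate among infants with known status, p/(1 − l), where l is the share lost:
- Control: 0.10/0.90 = 11.1%
- Exploration: 0.025/0.90 = 2.8%
- Difference: 8.3 points instead of 7.5; 0.0833/0.075 = 1.11

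A simulation (208 per arm, 20 imputations, 1,500 trials) agrees: mean difference 8.32 points after imputation v 7.49 with complete data, standard error 2.6 v 2.3 points.

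If a share q of all reoperations goes unrecorded, the rate is p(1 − q)/(1 − l). At q = 5% the difference is 0.075 × 0.95/0.90 = 7.9 points, 5.6% too large. At q = 10% the bias is zero.

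**Non-attendance unrelated to outcome, d = 10% in each arm.** Among infants with known status the rate is p[1 − d(1 − c)] / [1 − d(1 − p) − dp(1 − c)]. Expected numbers per arm, control / exploration:

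| c | Status missing | Reoperations truly missed | Reoperations imputed | Rates after imputation | Rates if nothing on record counts as no event |
|---|---|---|---|---|---|
| 0 | 20.8 / 20.8 | 2.08 / 0.52 | 2.08 / 0.52 | 10.0% / 2.5% | 9.0% / 2.25% |
| 0.5 | 19.8 / 20.5 | 1.04 / 0.26 | 2.07 / 0.54 | 10.5% / 2.6% | 9.5% / 2.4% |
| 1 | 18.7 / 20.3 | 0 / 0 | 2.06 / 0.56 | 11.0% / 2.8% | 10.0% / 2.5% |

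For any c above zero, more reoperations are imputed than were missed. For any c below 1, counting all unresolved infants as event-free errs the other way, so the two analyses bracket the truth.

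**Odds ratio.** The odds after imputation are p/(1 − p) × [1 − d(1 − c)]/(1 − d). With the same d and c in both arms the second factor cancels:
- True value: (0.025/0.975)/(0.10/0.90) = 0.231, unchanged for every c.
- Under the upper-bound assumption: (0.0278/0.9722)/(0.1111/0.8889) = 0.229.

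With unequal loss (hypothetical splits):
- At c = 1, with 15% lost in control and 5% in exploration: 0.231 × 0.85/0.95 = 0.206. With the reverse split: 0.231 × 0.95/0.85 = 0.258.
- Under the upper-bound assumption the same splits give 0.203 and 0.258.

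**Cost per reoperation prevented.** The denominator is inflated by up to 11%. No costs were modelled.

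**The case against.** Several objections carry weight.

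- **The article does not say in terms that reoperation status will be imputed.** The full-group denominator under Primary outcome measure could be read as recorded events over all infants, with nothing left to impute. The general rule in {20c} makes no such exception, though, so the two sections can lead to different analyses. The point rests on {20c} as written. An analysis plan that is not shown may narrow it.
- **A reader might infer that the absence of a named records check or sensitivity analysis is itself a defect.** It is not: a journal article commonly leaves such detail to the analysis plan. The defect is that the rule the article does state fits this endpoint badly.
- **A reader might infer that all imputed reoperations are spurious.** The document does not support that. Parents may leave the study at any time, and operations after withdrawal or at other hospitals may go unseen. Capture is not stated, and with none there is no bias.
- **A reader might infer that the primary result is biased.** The primary effect is the adjusted odds ratio, which hardly moves with equal loss. The document gives a single 10% figure and no split by arm. The open-label design makes unequal loss possible, but establishes neither its size nor its direction.
- **A reader might infer that the cost per reoperation prevented is 10% too low.** That would hold only with the cost difference fixed. Missing costs are imputed as well, so the numerator may change too.
- **Some safeguards exist.** A digital consult may replace the visit, infants withdrawn from treatment are asked back at 1 year, and a monitor checks data against source documents. These reduce the amount missing but do not change how the remainder is handled.
- **The shift is modest.** Even at full capture, 0.8 points is about a third of the 2.3-point standard error.

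**Conclusion.** The point holds in this limited form. If {20c} is applied as written to the primary outcome, and if at least some reoperations among lost infants are captured by the centres' routine recording, standard missing-at-random imputation overstates both reoperation percentages and their difference. At 10% equal loss the inflation runs from none (no capture) to 11.1% v 2.8% instead of 10% v 2.5% (full capture), that is 8.3 instead of 7.5 points. The effect denominator of the cost per reoperation prevented grows by up to 11%; the change in the ratio itself also depends on imputed costs and cannot be given from the document. The primary odds ratio is essentially untouched when loss and capture are equal in the two arms. At illustrative 15%/5% splits it would lie between 0.20 and 0.26 against 0.23. Importance is minor to moderate.

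**What to change.** In {20c}, for the primary outcome:

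1. For every infant without a 1-year contact, first obtain reoperation status and date from the participating centres' operation records and a telephone call to the parents, within the limits of consent. The trial already uses a call at 4 weeks.
2. Impute only infants still unresolved, conditional on being event-free at last contact.
3. Report alongside a sensitivity analysis that counts unresolved infants with no recorded reoperation as not reoperated.
4. Use the same outcome variable for the cost per reoperation prevented.

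Cost: 10% of 416 is about 42, so record checks or calls for about 40 infants, one extra analysis and a paragraph of text. No added visits or patients. The absolute effect may come out slightly smaller than under the present rule.

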### Plans to give access to the full protocol, participant level-data and statistical code {31c}

The trial protocol and statistical analysis plan will be made available via ‘figshare’. Completely deidentified datasets will be delivered to an appropriate data archive for sharing purposes and can be made available upon reasonable request and in agreement with our research collaboration and data transfer guidelines as stated in the Datamanagement plan.

## Oversight and monitoring

### Composition of the coordinating centre and trial steering committee {5d}

The HERNIIA trial is a multicentre study designed and coordinated in the Amsterdam UMC.

Principal investigator: responsible for all clinical research activities, thereby ensuring the study is conducted in accordance to the SOP and GCP guidelines.

Steering committee (see title page for members): assistance with the design of the study, agreement of final protocol and statistical analysis plan, reviewing progress of study and if necessary agreeing changes to the protocol.

Trial management committee (principal investigator, study coordinator and project leader): design and conduct of the trial, preparation of protocol and revisions, building the CRFs, study planning, trial registration, organisation of steering committee meetings, provide annual reports to ethics committees, (serious) adverse event ((S)AE) reporting, responsible for trial master file and site master files, contractual issues with participating centres, coordinating site visits, assistance with international review, board/independent ethics committee applications, data entry and verification, randomisation, publication of study reports, ensuring follow-up according to the protocol.

Lead investigators: in each participating centre a lead investigator is responsible for identification, recruitment, informed consent, data collection and completion of CRFs, along with follow-up of study participants and adherence to study protocol. They also assist in reviewing the progress of study and if necessary agreeing changes to the protocol.

### Composition of the data monitoring committee, its role and reporting structure {21a}

Both treatment strategies (unilateral hernia repair with contralateral exploration and unilateral hernia repair only) are currently performed in infants with unilateral inguinal hernia who need to undergo unilateral hernia repair. Consequently, there are no additional risks for subjects of this study and it is therefore not necessary to install a Data Safety Monitoring Board. Since this study is undertaken in infants and in order to make sure that the potential risks and burden of contralateral exploration does not outweigh the potential benefits, we installed an independent safety committee, that will provide assurance that the rights, safety and well-being of trial subjects are protected, and will monitor all complications and judge how to continue if a (S)AE is encountered.

### Adverse event reporting and harms {22}

All adverse events reported spontaneously by parents of the subject or observed by the investigator or his staff will be recorded from the start of the study until the moment of first follow-up. If a life-threatening SAE likely related to the study is encountered, this SAE will immediately be reported to the Central Committee on Research Involving Human Subjects (CCMO) according to the CCMO guidelines, and the study will be paused instantly, if appropriate. Inguinal hernia repair is usually at most accompanied by minimal complications.

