## Abstract

**Background:**

The incidence of metachronous contralateral inguinal hernia (MCIH) is high in infants with an inguinal hernia (5–30%), with the highest risk in infants aged 6 months or younger. MCIH is associated with the risk of incarceration and necessitates a second operation. This might be avoided by contralateral exploration during primary surgery. However, contralateral exploration may be unnecessary, leads to additional operating time and costs and may result in additional complications of surgery and anaesthesia. Thus, there is no consensus whether contralateral exploration should be performed routinely.

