#### Complications of anaesthesia and surgery

Complications related to inguinal hernia within 1 year after primary repair are as follows: wound infection, hematoma, hydrocele, testicular atrophy, apnoea or inguinal hernia recurrence. Apnoea, wound infection, hematoma and hydrocele will be assessed during hospital admission via monitoring (if applicable) and by the (fellow) paediatric surgeon. After hospital discharge, these complications will be assessed through a phone call performed by one of the investigators 4 weeks following surgery. Testicular atrophy and inguinal hernia recurrence will be assessed at the outpatient clinic 1 year following surgery. If there is partial or complete testicular atrophy of one testis (i.e. one of the testes is smaller compared to the other at follow-up), additional ultrasonography of both testes will be performed. Complications are defined as:
Testicular atrophy: No palpable testicular tissue in scrotum (=complete testicular atrophy) or testis documented to be smaller at follow-up than at time of inguinal hernia repair (=partial testicular atrophy) at operated side(s).Wound infection/surgical site infection: Infection occurring within 30 days of surgery; infection involving only the skin and subcutaneous tissue; at least one of the following: (a) purulent discharge from a superficial infection or (b) organisms isolated from aseptically obtained wound culture; and at least one of the following signs of infection: (a) pain or tenderness, (b) localised swelling and (c) redness or hyperthermia [24].Apnoea: Apnoea of infancy is defined as “an unexplained episode of cessation of breathing for 20 seconds or longer, or a shorter respiratory pause associated with bradycardia, cyanosis, pallor, and/or marked hypotonia requiring intervention”. Types of interventions recorded will include stimulation, assisted ventilation, continuous positive airway pressure (CPAP), endo-tracheal intubation and administration of methylxanthine [25].Recurrence: the hernia returns at the previously operated side and a reoperation on the same side is warranted.

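### General adverse event recording stops at an undefined first follow-up and incarceration of an MCIH is no named outcome, so some late harms, expected mainly in the control arm, are not reported as harms

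*Protocol article*

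**What the plan says.** Under *Adverse event reporting and harms {22}*, all adverse events, whether volunteered by parents or seen by staff, "will be recorded from the start of the study until the moment of first follow-up". The article does not say which contact that is.

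Four other places bear on the window:

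- *Complications of anaesthesia and surgery* (secondary outcomes) opens with "Complications related to inguinal hernia within 1 year after primary repair are as follows" and gives a closed list: "wound infection, hematoma, hydrocele, testicular atrophy, apnoea or inguinal hernia recurrence". Incarceration is not on it. After discharge, apnoea, wound infection, hematoma and hydrocele are covered in this way: "these complications will be assessed through a phone call performed by one of the investigators 4 weeks following surgery". Testicular atrophy and recurrence are assessed at 1 year.
- *Post intervention assessment* schedules outcomes to be "assessed during hospital admission, 4 weeks after primary hernia repair and 1 year after primary hernia repair". For infants with MCIH it adds that "baseline and outcome assessments will also be performed during and 4 weeks after MCIH repair".
- *Composition of the data monitoring committee {21a}* sets up an independent safety committee that "will monitor all complications and judge how to continue if a (S)AE is encountered".
- The abstract gives part of the rationale: "MCIH is associated with the risk of incarceration and necessitates a second operation". *Baseline assessment* and *Plans for assessment and collection of outcomes {18a}* collect incarceration only as a preoperative hernia characteristic.

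**The concern.** The trial weighs the extra burden of exploring the second groin against the harm of leaving it alone. These harms arise at different times. Those of exploration arise mostly around the primary operation, inside any early adverse event window. Those of not exploring arise when an MCIH appears, which can be at any point in the year.

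A general record that closes at about 4 weeks, with a closed complication list lacking incarceration, leaves part of the second kind without a place to be reported. An MCIH that presents as an emergency and one repaired electively each count as one reoperation in the primary outcome, and no named outcome separates them. Incarceration is a stated reason for considering exploration, so the trial could end without reporting how often exploration prevented it. The *Discussion* also says that the burden of the intervention will be judged partly from adverse event information, and the *Economic evaluation* costs the treatment of complications. Both may inherit the gap.

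**Working it through.** **Step 1: the windows side by side.**

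| Section of the article | What is recorded | Until when |
|---|---|---|
| Adverse event reporting {22} | all adverse events | first follow-up, undefined |
| Complications (secondary outcome) | six listed items | 1 year after primary repair |
| Post intervention assessment | primary and secondary outcomes | admission, 4 weeks, 1 year; also at MCIH repair and 4 weeks later |
| Data monitoring committee {21a} | all complications | no end stated |

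The first scheduled contact after discharge is at 4 weeks. If that is first follow-up (an assumption), the general window covers 28/365 = 7.7% of the year after surgery and leaves about 92% outside.

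**Step 2: which late events have a place in the record.**

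- Apnoea, wound infection, hematoma or hydrocele at an MCIH repair: yes, through the repeated assessments.
- Testicular atrophy and recurrence: yes, at the 1-year visit.
- The second operation itself: yes, it is the primary outcome. Its anaesthesia time and hospital stay are also recorded.
- Incarceration or emergency presentation of an MCIH: not a named outcome or listed complication. Baseline assessments are repeated at MCIH repair and include history of incarceration, so it may be picked up indirectly, but the text does not say so.
- Unlisted adverse events and SAEs after first follow-up, including around a second operation: no stated recording.
- Complications around a reoperation for recurrence: the repeat assessment is stated for MCIH repair only, although the primary outcome counts any reoperation related to inguinal hernia.

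**Step 3: the plan's sample size, to fix the number per arm.** Inputs from *Sample size {14}*: 10% against 2.5%, power 0.80, two-sided alpha 0.05. The mean proportion is 0.0625.

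n = [1.96·√(2·0.0625·0.9375) + 0.8416·√(0.10·0.90 + 0.025·0.975)]² / 0.075² = (0.671 + 0.285)² / 0.005625 ≈ 162.3, so 163 per arm without continuity correction.

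With the correction: (162.3/4)·[1 + √(1 + 4/(162.3·0.075))]² ≈ 188.1, so 189 per arm and 378 in total. This matches the plan, and the figure is not in dispute.

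**Step 4: how many infants the gap could concern.**

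- Reoperated infants: control 189 × 0.10 = 18.9; exploration 189 × 0.025 = 4.7.
- The *Background* reports an incarceration risk of 3–30% in the first 6 months of life. Applied to MCIH (an assumption):
  - control 18.9 × 0.03 = 0.6 to 18.9 × 0.30 = 5.7;
  - exploration 4.7 × 0.03 = 0.1 to 4.7 × 0.30 = 1.4.
- With 208 per arm (416/2): 20.8 and 5.2 reoperated, giving 0.6–6.2 and 0.2–1.6.

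For scale, the *Background* gives wound infection, a listed complication, as 0.6–1.2%. At 189 infants that is 1.1–2.3 per arm. The control-arm range for incarceration begins below this and ends above it.

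Apnoea at a second anaesthesia, at the quoted upper figure of 12%, would be 18.9 × 0.12 = 2.3 against 4.7 × 0.12 = 0.6. By Step 2 these fall inside the record at MCIH repair and are not part of the gap.

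**The case against.** The strongest reply is that the randomised comparison does not rest on the general adverse event log. The main harm of waiting, a second operation within the year, is the primary outcome. Operation and anaesthesia time, hospital stay, the listed complications, quality of life, parental distress and costs are also followed for the year. All of this stands, and it rules out three stronger conclusions that a reader might draw:

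- *That harms of the second anaesthesia go largely unrecorded.* The repeated assessments at MCIH repair cover the listed ones, apnoea included.
- *That the whole benefit-harm comparison is biased against exploration.* Most of the relevant outcomes run for 1 year in both arms. Only incarceration and unlisted events are affected.
- *That the safety committee sees nothing after 4 weeks.* Its remit is all complications, and the listed ones run to 1 year. Reporting of life-threatening related SAEs also carries no stated end date.

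It is also fair that first follow-up may not mean the 4-week phone call, since the article also uses follow-up for the 1-year assessment. Nor does the article give a time distribution for MCIH, and the 3–30% is quoted for hernia in the first 6 months of life, while an MCIH may arise later. The counts are therefore illustrative.

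Finally, this is a condensed article, and the full protocol may hold more detail on adverse events. That would excuse silence. Here, however, the article states a stopping rule that does not fit its own other sections, and a closed list that leaves out an event central to its rationale.

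**Conclusion.** The point holds in a limited form. The adverse event window conflicts with the 1-year complication window, the repeat assessments at MCIH repair and the safety committee's remit, and these sections must be reconciled. Followed as written, the plan does not report incarceration or emergency presentation of an MCIH as a harm, and does not provide for recording unlisted adverse events and SAEs after first follow-up.

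The gap differs by arm because reoperation is expected mainly in controls, about 19 against 5 infants. The incarcerations not reported as harms would number about 0.6–5.7 against 0.1–1.4, although any that are operated on remain in the primary outcome. This rests on three assumptions: first follow-up is the 4-week contact, the planning rates hold, and the 3–30% risk carries over to MCIH. The conflict between the sections and the omission of incarceration depend on none of them. No stated figure and no primary analysis is affected.

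**What to change.** 1. Define first follow-up, and bring the adverse event section into line with the complication, post-intervention and safety committee sections.
2. Record SAEs, and adverse events related to the hernia, surgery or anaesthesia, until the 1-year visit, and until 4 weeks after any inguinal hernia reoperation, including one for recurrence.
3. Add incarceration or emergency operation of any inguinal hernia within 1 year as a reported secondary complication, by arm. For infants already enrolled, take it from the reoperation record and the 1-year visit.

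The cost is a protocol amendment, one eCRF item at contacts that already exist, and slightly more SAE reporting. By the article's own status (302 included in August 2021, inclusion expected to end in March 2022, a year of follow-up after that), there was still time to collect the item prospectively for many participants.
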